#### 2.6.2. MCT Group Intervention Description

The participants of the control group will only perform the MCT during the 8 weeks, totaling 24 sessions, following the same descriptions of the MCT of the GTMV group.

#### 2.6.3. Discontinuity Criteria

Participants who have three consecutive absences during the 8-week intervention period, as well as those who no longer wish to participate in the study, will be discontinued from the study. Patients who are discontinued from the study will be included in the intention-to-treat analysis.

#### 2.6.4. Treatment Adherence

Some strategies will be adopted to guarantee the adherence and attendance of these participants, such as constant communication with the patient to clarify doubts, possible questions and guidance about the OST and the risk of falls; individualized monitoring of sessions, with scheduled service, motivating the participant to complete the total number of sessions.

### 2.7. Outcome Assessments

The following variables will be collected to establish the general characteristics of the sample: weight, height, Body Mass Index (BMI), sex, marital status, place of birth, education, occupation, family income, number of chronic conditions, use of medications, and frequency of falls in the last year.

#### 2.7.1. Primary Results

Assessment of the risk of falls was performed using the Falls Efficacy Scale International (FES I), an instrument validated for the Brazilian elderly [35]. The internal consistency of the FES-I Brazil was α = 0.93, and the reliability was ICC = 0.84 and 0.91 (intra- and inter-examiners, respectively). A 16-item questionnaire will be answered on a four-point Likert scale (1 = not at all worried, 2 = a little worried, 3 = very worried 4 = extremely worried), totaling 16 items scored on a four-point scale (1 = not at all worried 4 = very worried) [36,37]. This should be reliable to assess fear of falling in older women at higher risk of falling and that the FES I score should change by >3 points or 11% to identify clinical change over time at the group level and the individual level, the sum of the score would have to change by >8 points or 29% [38].

Quality of life will be measured using the WHOQOL-OLD, validated for Portuguese. It comprises 24 items recorded on a five-point Likert scale, divided into six facets: “sensory functioning”, “autonomy”, “past, present, and future activities”, “social participation”, “death and dying”, and “intimacy”. The instrument’s overall score determines that higher scores represent better quality of life in the facets. The instrument has satisfactory characteristics of internal consistency (Cronbach’s coefficients from 0.71 to 0.88), discriminant validity (*p* < 0.01), concurrent validity (Correlation coefficients between −0.61 and −0.50), test–retest reliability (Correlation coefficients between 0.58 to 0.82), usefulness, and good psychometric performance [39,40]. The minimal clinically important differences for quality-of-life measures are variable depending on the method applied and the clinical context of the study [41].

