**Abstract:**

Osteoporosis and the risk of falls increase the risk of fractures and events of falls. Prescriptions and programs for different forms of exercise have different impacts on the risk of falls, and exercises from multiple categories of whole-body vibration can be effective. This study aims to evaluate the effectiveness of whole-body vibration (WBV) protocol combined with multicomponent training (MCT) in elderly women with osteoporosis and their history of falls. Our proposal is a protocol for a randomized clinical trial, divided into two stages: First, development of a protocol for WVB combined with MCT for elderly women with osteoporosis and a history of falls, under the Guidelines of the American College of Sports Medicine, and following the recommendations of the Standard Protocol Items Recommendations for Interventional Trials (SPIRIT), and second, a randomized controlled clinical trial following the Consolidated Standards of Reporting Trials (CONSORT). This trial will have implications for the effectiveness of a vibration protocol combined with multicomponent exercise on the risk of falls and quality of life for older women with osteoporosis. We expect that adding full-body vibration to an exercise protocol will decrease the risk of falls and improve participants’ quality of life, as well as their strength, balance, and functional capacity.

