Another therapeutic modality used in people with OST is whole-body vibration (WBV), a non-invasive and non-pharmacological intervention that can promote a reduction in the impact on bone mass and density, helping to gain balance and muscle strength and reducing the number and risk of falls [20,21,22,23,24]. WBV alone or in combination with exercise can also decrease the number of falls and the risk of falls, being essential to prevent bone fractures and osteoporosis [21,22,25].

In clinical practice, protocols with the prescription of multicomponent exercises and vibration in the elderly and patients with osteoporosis are described in isolation or combination during the use of the platform. To our knowledge, no studies have been found using WBV combined with MCT in elderly women with OST, in which the protocol contained detailed information on parameters, frequency, and duration, among others, necessary for clinical reproducibility. Given the above, the present study aims to develop a protocol for a clinical trial to verify the efficacy of WBV combined with MCT in the risk of falls and the quality of life of elderly women with OST.

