#### 2.7.2. Secondary Results

The secondary outcomes will be measured to assess the participants’ functional capacity: balance, lower limb muscle strength, functional gait mobility, and global perception of the protocol. Treatment adherence and adverse events will also be analyzed.

The balance will be assessed using the functional range test (FRT). A reliable and valid measure of balance, which measures the ability to advance in an anticipatory postural adjustment task [42,43]. The test consists of asking the subject to stand with the right shoulder close to a wall, performing an anterior flexion of the arm at 90º, with the fingers of the hands in flexion; then, the length of the right upper limb will be registered on the ruler. After this procedure, the subject is asked to try to reach some object in front of him without taking steps or performing any compensatory strategy [44]. When developing the test, established as normative values for men 33.4 ± 3.9 cm and women 26.5± 8.9 cm [42] and in a recent meta-analysis, [44] Rosa, Perracini, and Rici (2019) determined as normative for the community elderly population values of 26.60 cm (CI 95%: 25.14–28.6 cm), while for the Brazilian population [45] established that women between 41–69 years have a mean RF of 28.54 (SD 3.61) and between 70–87 years have a mean of 27.13 (SD 2.83).

The dynamic balance of the participants will also be evaluated through the Biodex Balance System platform (Biodex Medical, USA) in the Falls Risk Test (FRt) protocol, the platform is unstable and estimates the fall risk index. The protocol is composed of 12 levels of dynamic stability with level 12 being the most rigid and level 1 being the most unstable. The participant will be instructed to stay on the platform: standing, barefoot, and with eyes open. They should maintain a vertical projection with their center of gravity in the center of the platform, observing a vertical screen located in front of their face, then the average result of three tests will be obtained, each evaluation will last 20 s, with rest periods of 10 s between them. The test will generate a General Stability Index (IGE)/Overall stability index (OSI), i.e., the total variation of the displacement from the center of the platform through the general variation of the Anterior–Posterior Stability Index (APSI) and the Medial–Lateral Stability Index (MLSI) [46,47].

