## 3. Discussion

To determine the efficacy of WBV combined with MCT in women with osteoporosis and a previous history of falls, an intervention study will be conducted. It is assumed that adding vibration to MCT will decrease the risk of falling and improve the quality of life of the participants.

Models of care for OST include fractures, assessments, education, and exercise programs [10]. Bone health is essential for the elderly and concerning OST, recent evidence indicates that exercise can delay its onset and reduce the risk of falling [26].

A meta-analysis of patients with OST (RR 0.832; CI 0.762–0.909; n: 3569 participants; 10 randomized clinical trials; I2 = 13.4%) observed the effects of exercise in fall-related injuries, thus demonstrating that participants at high risk of falls or with OST would benefit primarily from exercise intervention [8].

Different pieces of evidence bring the importance of exercises and WBV. However, to date, there are few studies with WBV programs added to multicomponent exercises, aimed at improving the risk of falls and the quality of life of women with OST, among these, a randomized clinical trial [58] (n:42 elderly) of a vibration protocol added to exercise on the risk of falls and quality of life observed improvements in balance, gait, and quality of life in the participants undergoing the intervention. In turn [59] in a randomized clinical trial (n:77 elderly) of WBV added to the strength and balance exercises found that the improvement in functional mobility of this WBV addition was greater than in the group that performed the exercise alone.

The MCT refers to the combination of three or more training modalities that involve exercises that involve muscular endurance, aerobic, balance, and flexibility exercises in the same training session [30,60,61]. Given the above, a multicomponent exercise program is recommended to improve physical fitness and reduce the incidence and risk of falls in the elderly [62].

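### The primary outcome labelled as risk of falls is FES-I, which the protocol itself describes as a fear-of-falling scale, so an FES-I difference supports a conclusion about concern about falling only

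*Protocol article*

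**What the plan says.** **Label.** Section 2.7.1 (Primary Results) opens with "Assessment of the risk of falls was performed using the Falls Efficacy Scale International (FES I").

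**Description of the scale.** The same paragraph gives the response format as a "four-point Likert scale (1 = not at all worried, 2 = a little worried, 3 = very worried 4 = extremely worried"), applied to 16 items. On the scale's use it says: "This should be reliable to assess fear of falling in older women at higher risk of falling". Its change thresholds, more than 3 points (11%) for a group and more than 8 points (29%) for an individual, appear in that sentence.

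**Aim and expectation.** The Introduction states the aim as "to verify the efficacy of WBV combined with MCT in the risk of falls and the quality of life of elderly women with OST". The Abstract says "We expect that adding full-body vibration to an exercise protocol will decrease the risk of falls" and the Discussion says "It is assumed that adding vibration to MCT will decrease the risk of falling". Section 4 (Conclusions) again presents reducing the risk of falls as the purpose.

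**Sizing.** Section 2.8 bases the sample size on FES-I, with a between-group change of more than 2.9 points as the clinically relevant difference.

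**Other measures.** WHOQOL-OLD is also listed under Primary Results. The Biodex Falls Risk Test is a secondary outcome under dynamic balance, of which section 2.7.2 says "the platform is unstable and estimates the fall risk index". Among the variables describing the sample, section 2.7 lists "frequency of falls in the last year". Neither the outcome sections nor the schedule in Table 3 lists falls after randomisation.

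**The concern.** How worried a woman is about falling and how likely she is to fall are different quantities. Section 2.7.1 names one and measures the other. If the label stands, a favourable FES-I result will be read as evidence that vibration lowers fall risk, although the instrument records neither falls nor a probability of falling.

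The distinction matters in this design. FES-I is self-reported, and under section 2.6.2 the control group performs the exercise programme only. Participants will presumably know whether they used the platform, so expectation could shift reported worry without any change in fall risk. The point does not depend on this, but it shows why the two constructs should not be merged. Section 4 expects the results to bear on clinical practice and health policy, where the difference between less worry and fewer falls is material.

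**Working it through.** No arithmetic decides this. The article gives no sample size or standard deviation to reproduce, and the point concerns what the instrument measures. The check is to set the relevant statements side by side.

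1. **Label against description.** Section 2.7.1 assigns FES-I to risk of falls, then says it assesses fear of falling in women at higher risk of falling. In that sentence fear is what is measured and risk is a separate attribute of the women. The two are not used as synonyms.

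2. **What the score contains.** Sixteen items scored 1 to 4 give a total from 16 × 1 = 16 to 16 × 4 = 64. Every point is a step in worry. The thresholds of more than 3 and more than 8 points, and the 2.9 points in section 2.8, are differences on this scale. The article relates none of them to a fall probability or rate.

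3. **How the article otherwise uses risk of falls.** The Introduction supports the trial with event data: a risk ratio for falls of 0.88, a rate of falls lower by 34% (rate ratio 0.66, and 1 − 0.66 = 0.34), and 22% fewer people who fall (risk ratio 0.78, and 1 − 0.78 = 0.22). A reader who carries that usage forward will take the primary result to concern falls.

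4. **Is there a bridging statement?** I found none. No section says that a change in FES-I predicts, or is accepted as a surrogate for, a change in fall risk or fall rate.

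5. **Does another measure fill the gap?**
   - WHOQOL-OLD, the other primary outcome, measures quality of life.
   - The Biodex test is scheduled in Table 3 at baseline, t1, t2 and t3. Section 2.7.2 defines its output as a stability index, built from displacement from the platform centre. It is a balance measure, and no relation to fall probability is given.
   - Knee-extension strength is justified in section 2.7.2 as helping to identify people at high risk. It is also a secondary proxy.
   - Fall frequency is collected for the year before entry, to describe the sample.
   - Section 2.7.2 counts adverse effects from the researcher's record but does not say whether falls are entered there, in sessions or at home.

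The label in section 2.7.1 is therefore contradicted by its own paragraph, and nothing else at primary level measures fall risk.

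**The case against.** Four points can fairly be made on the other side.

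- **The wording states aims and expectations.** The Abstract expects, the Discussion assumes, and the Conclusions describe what the protocol seeks. A reader might infer that the trial has committed itself to reporting a significant FES-I difference as lower fall risk. No section says so. The label makes that misreading likely, but it is not a written reporting rule.
- **The trial is not silent on fall risk.** A reader might infer that it holds no information on the subject. The Biodex test and extensor strength are both measured and both bear on it indirectly. What remains is that they are secondary proxies, not the measure the trial is sized on.
- **The Biodex index might seem a ready substitute.** Its name suggests it could carry any statement about fall risk. The article describes a postural stability index, so this would replace a fear proxy with a balance proxy.
- **The FES-I comparison remains sound.** The mislabelling does not invalidate the randomisation, the measurement or the choice of FES-I as sizing endpoint. The result is still evidence about concern about falling, and the quality-of-life outcome is untouched.

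All four stand and limit the point. None removes the contradiction within section 2.7.1. Nor is it a detail left to an analysis plan, because the article states what the primary outcome measures and states it wrongly.

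**Conclusion.** The point holds in a limited form. FES-I is labelled as risk of falls but described as a measure of fear of falling, with no stated link from one to the other. A between-group FES-I difference supports a conclusion about concern about falling. It does not support the lower risk of falls named in the aim, the expectation and the conclusions.

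The size is qualitative: one of two primary outcomes is affected, and it is the one on which the sample size is based. The conclusion rests on the article's own description of FES-I and on the absence of any bridging statement in it. If the full protocol justifies FES-I as a surrogate for fall risk, that justification would need to be stated and assessed.

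The correction should be made before results are reported, since relabelling afterwards could look driven by the data.

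**What to change.** 1. In section 2.7.1, the aim, the hypothesis and the conclusions, name this primary outcome *concern about (fear of) falling, FES-I*, and limit conclusions drawn from it to that construct. Leave WHOQOL-OLD as it is.
2. Report the Biodex Falls Risk Test, already scheduled at every assessment, as a secondary balance-based proxy (postural stability index), not as evidence of fewer falls.
3. Report falls during the 8 weeks by arm, descriptively, only to the extent that the adverse-effects record captures them. The article does not say that it does, so a usable count may need ascertainment that is not now described.

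**Cost.** The headline claim becomes narrower, and the outcome wording of a registered trial must be updated. Steps 1 and 2 need no new measurement; step 3 might, if a complete fall count is wanted. If the sponsor prefers to keep fall risk as the primary question, the alternative is to make a fall-risk measure or prospectively recorded falls the primary outcome and size the trial on that, which is a much larger change.

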#### 2.7.2. Secondary Results

The secondary outcomes will be measured to assess the participants’ functional capacity: balance, lower limb muscle strength, functional gait mobility, and global perception of the protocol. Treatment adherence and adverse events will also be analyzed.

The balance will be assessed using the functional range test (FRT). A reliable and valid measure of balance, which measures the ability to advance in an anticipatory postural adjustment task [42,43]. The test consists of asking the subject to stand with the right shoulder close to a wall, performing an anterior flexion of the arm at 90º, with the fingers of the hands in flexion; then, the length of the right upper limb will be registered on the ruler. After this procedure, the subject is asked to try to reach some object in front of him without taking steps or performing any compensatory strategy [44]. When developing the test, established as normative values for men 33.4 ± 3.9 cm and women 26.5± 8.9 cm [42] and in a recent meta-analysis, [44] Rosa, Perracini, and Rici (2019) determined as normative for the community elderly population values of 26.60 cm (CI 95%: 25.14–28.6 cm), while for the Brazilian population [45] established that women between 41–69 years have a mean RF of 28.54 (SD 3.61) and between 70–87 years have a mean of 27.13 (SD 2.83).

The dynamic balance of the participants will also be evaluated through the Biodex Balance System platform (Biodex Medical, USA) in the Falls Risk Test (FRt) protocol, the platform is unstable and estimates the fall risk index. The protocol is composed of 12 levels of dynamic stability with level 12 being the most rigid and level 1 being the most unstable. The participant will be instructed to stay on the platform: standing, barefoot, and with eyes open. They should maintain a vertical projection with their center of gravity in the center of the platform, observing a vertical screen located in front of their face, then the average result of three tests will be obtained, each evaluation will last 20 s, with rest periods of 10 s between them. The test will generate a General Stability Index (IGE)/Overall stability index (OSI), i.e., the total variation of the displacement from the center of the platform through the general variation of the Anterior–Posterior Stability Index (APSI) and the Medial–Lateral Stability Index (MLSI) [46,47].

Muscle strength will be assessed using the 1 Repetition Maximum (1 RM) test, which has been considered a standard for the assessment of dynamic strength [26,48,49], with adequate familiarization being a reliable indicator of muscle strength [50]. The test will be carried out in a fixed muscle-strengthening device (Mega II Movement), if necessary, also using dumbbells (to adapt the gradation of smaller loads), and the maximum amount of weight lifted will be recorded during the performance of the extension exercise, given that the strength of the extensors is a good measure to identify elderly people at high risk of falls [51].

To assess functional capacity, the distance walked in the 6-min walk test (6MWT) will be used, which adequately reflects the physical capacity of patients to perform routine tasks. The test will be carried out in an external corridor, 30 m long, with a smooth surface marked meter by meter, in which the patient must go and return as often as possible during the pre-established time. The circuit delimitation will be indicated by signaling cones. Immediately before starting the tests, participants will receive guidance, following the standardization suggested by the American Thoracic Society (ATS) [52,53,54]. For the Brazilian population, the authors investigated predicted values to determine the distance covered by a Brazilian population of adults and elderly people, which is represented by: 6MWD = 622.461−(1.846 × age) + (61.503 × male gender = 1, women = 0) and the MCID estimate for 6MWD adopted is 17.8 m when analyzing changes in interventions in moderately frail Asian elderly with fear of falling after an exercise protocol [55].

The global impression of patients will be assessed by the Patient Global Impression of Change (PGIC), adapted and validated for the Portuguese population [56]. This is an understandable, adequate, easy, and quick use instrument, being an aid in the comparison of results between interventions and/or in identifying clinically important differences. It is a one-dimensional measure in which users rate their improvement combined with the intervention on a seven-item scale ranging from “no change (or the condition got worse)” to “much better, and with a considerable improvement that made all the difference” [57].

Adherence will be calculated by the percentage of sessions completed out of the total number of prescribed intervention days (24 sessions = 100%), reported by the researcher. Adverse effects will be counted from the researcher’s record.

After the initial assessment, baseline (t0), there will be three moments for reassessment: after the 8th session (t1), 16th session (t2), and 24th session (t3).

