### 2.2. Participants

Participants will be recruited from the local community. Inclusion criteria are: (1) Elderly women over 60 years old with OST (diagnosed with Bone Densitometry Exam); (2) history of falls (at least two episodes in the last 12 months); (3) medical statement allowing the practice of physical exercise (cardiologic statement); (4) not participating in other research studies. Patients with: (1) Neurological diseases; (2) cognitive deficit (cognitive ability to respond and perform the exercises assessed by the Mini-Mental State Examination; MMSE), elaborated [26] and translation/modification proposed [27], using as a cutoff point for illiterate individuals = 19 points [28,29]; (3) severe Visual Impairment; (4) circulatory diseases; amputation or use of lower limb prosthesis; (5) history of recent fracture in the upper and lower limbs; (6) hernia, discopathy or severe spondylosis; and (7) neoplasm.

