### 2.5. Blinding

Outcome assessments will be performed by three researchers who are blind to the intervention group to which the participant was allocated. Statistical analysis will also be performed by a researcher who is blind to other research procedures.

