### 2.6. Intervention

The intervention protocol will be applied by an experienced physical therapist, blind to the assessment of outcomes, soon after the enrolment period. It will consist of 8 weeks of training for both groups, totaling 24 sessions distributed three times a week, on alternating days. Each session will last between 45 and 48 min, depending on the participant’s group (Table 3).

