**Assessments**						
FES-I	x		x	x	x	
WHOQOL-OLD	x		x	x	x	
FRT	x		x	x	x	
FRt (BBS)	x		x	x	x	
IRM	x		x	x	x	
DTC6	x		x	x	x	
PGIC					x	
Adhrence			x	x	x	
Adverse effects			x	x	x	

Legend: after the 8th session (t1), 16th session (t2), and 24th session (t3).

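### Adverse effects are counted from an unspecified researcher's record with no described questioning about events between sessions, so falls and fractures outside sessions can be under-recorded

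*Protocol article*

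**What the plan says.** Section 2.7.2 of the protocol article places harms among the analysed outcomes: "Treatment adherence and adverse events will also be analyzed". Later in the same section the method is given: "Adverse effects will be counted from the researcher", the sentence going on to name that person's record. The sentence before it has session attendance reported by the researcher as well, also in the singular.

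Table 3 carries a row labelled "Adverse effects" under its assessments, marked at t1, t2 and t3 (after the 8th, 16th and 24th sessions).

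On who knows the arm, section 2.5 says "Outcome assessments will be performed by three researchers who are blind to the intervention group to which the participant was allocated". Section 2.6 says "The intervention protocol will be applied by an experienced physical therapist, blind to the assessment of outcomes". Section 2.6.2 says "The participants of the control group will only perform the MCT during the 8 weeks, totaling 24 sessions", and no sham platform is described.

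On falls, section 2.2 requires a "history of falls (at least two episodes in the last 12 months". Section 2.7 lists the past year's fall frequency as a sample characteristic. Neither sections 2.7.1 and 2.7.2 nor Table 3 lists a count of falls or fractures during the trial.

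**The concern.** The article does state a method here, so this is a question about the method chosen and not only about missing detail. A record that depends on what a researcher sees, or happens to be told, is passive. In women with osteoporosis who fall repeatedly, the harms of most interest are falls and fractures, and these will mostly happen away from the clinic. If nobody asks about them in a fixed way, some may never be written down.

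Two consequences follow. Missed events make both programmes look safer in absolute terms than they are. And if the chance of an event being written down differs by arm, the comparison of vibration plus training with training alone is distorted. That difference is possible because the recorder's identity and blinding are not stated for this item.

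Discontinuation adds to the risk. Three consecutive absences end participation (section 2.6.3), and reassessments are tied to session numbers. A woman who is injured at home and stops coming may leave no trace in a session-based record, and including her in the intention-to-treat analysis does not recover an event that nobody recorded.

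**Working it through.** The article gives no adverse event rate, no sample size and no power for harms, so there is no stated figure to reproduce. The arithmetic below is illustrative.

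**1. Supervised time**

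- Inputs (section 2.6): 24 sessions of 45 to 48 minutes, over 8 weeks.
- 24 × 45/60 = 18.0 h and 24 × 48/60 = 19.2 h.
- Total time: 8 × 7 × 24 = 1,344 h.
- Share: 18.0/1,344 = 1.3% and 19.2/1,344 = 1.4%.
- Assuming 16 waking hours a day, 8 × 7 × 16 = 896 h, and the share is 2.0% to 2.1%.

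This is the share of hours under direct observation. It is not the share of events that would be recorded.

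**2. Falls to be expected**

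- Input (section 2.2): at least 2 falls in 12 months. Assumption: this minimum rate continues, with Poisson counts.
- Expected falls per woman in 8 weeks: 2 × 56/365 = 0.31.
- Probability of at least one fall: 1 − exp(−0.307) = 26%.
- If the rate halved (assumption): 0.307/2 = 0.15 falls per woman.

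Given step 1, most of these would occur outside sessions. The figure is occurrence, not the number missed.

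**3. What incomplete recording does to the comparison**

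Let d1 and d2 be the proportions of true events recorded in the two arms.

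- Observed ratio = true ratio × d1/d2.
- If d1 = d2 = d, observed absolute difference = d × true difference.

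With a true ratio of 1 and assumed detection proportions:

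| d1 | d2 | Expected observed ratio |
|---|---|---|
| 0.5 | 0.5 | 1.0 |
| 0.3 | 0.3 | 1.0 |
| 0.8 | 0.5 | 1.6 |
| 0.5 | 0.8 | 0.63 |

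Equal detection of 0.5 halves the absolute difference and leaves the expected ratio alone. Unequal detection moves the ratio either way. The article gives nothing from which d1 or d2 could be estimated.

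**4. Who records**

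- For a blinded recorder: section 2.5 gives outcome assessments to blinded researchers, and Table 3 puts adverse effects under assessments. The article calls the assessors researchers and the person delivering sessions a physical therapist.
- For an arm-aware recorder: the researcher in section 2.7.2 also reports attendance, which suggests someone present at sessions, and anyone there sees whether the platform is used. Adherence, itself a tally of sessions, has the same t1 to t3 marks in Table 3, so the marks fit a tally of the record just as well.

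The text does not decide between these readings.

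**The case against.** The strongest reply is that this is a condensed article. Event definitions, the recording form and the wording of any question are commonly left to the full protocol, so their absence alone is not a fault. Women attend three times a week, and section 2.6.4 plans constant communication with them, so an event at home could be mentioned within days. The blinded assessors may already be the ones asking. Much of this stands: under-recording is a risk and not a certainty. What it does not meet is that the article commits to one named source, and that the contacts in section 2.6.4 serve adherence and are not a fixed enquiry about harms.

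Four stronger readings are tempting and are not supported:

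- *The recorder is known to be aware of the arm.* The text leaves this open, as step 4 of the working shows.
- *Counting effects means someone judges causality first.* Section 2.7.2 also says events, no causality step is described, and the article is loose with terms elsewhere. The two words should be harmonised, but the switch proves nothing.
- *Only 1.3% to 1.4% of events would be seen.* That is the share of hours. A record kept at 24 contacts can also hold anything a woman reports.
- *The conclusions claim safety on the strength of this count.* Section 4 speaks of safety as something the programme hopes to secure, and does not rest it on the adverse effect data.

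Nor does the slightly longer vibration session settle a direction of bias: the difference is 48 − 45 = 3 minutes per session.

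**Conclusion.** The point holds as a moderate weakness in how harms are collected. The only source named is a record kept by an unidentified researcher, no questioning about events between sessions is described, and no count of falls or fractures on trial is listed, in a population selected for osteoporosis and repeated falls. About 0.31 falls per woman over 8 weeks, or 26% of women with at least one, indicates how much there is to record; it assumes Poisson counts at the minimum entry rate. The number that would be missed cannot be worked out from the article.

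The effect on the comparison is conditional. Under-recording that is the same in both arms lowers the counts and the absolute difference, and costs precision, without biasing the ratio. Recording that differs by arm biases the ratio, in a direction that the article does not allow one to predict.

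**What to change.** Count adverse events whatever their presumed cause, and use that one term in both places in section 2.7.2 and in Table 3. Any judgement of relatedness should come only after the event is recorded.

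At t1, t2 and t3, where Table 3 already marks the item, have the blinded assessors put the same short fixed question to both arms: any fall, fracture, new pain or other health event since the last visit, in or out of sessions. State who keeps the session record and whether that person knows the arm, and report that record separately as a second source. Questions asked at visits reach only women still attending, so say how the same question will be put to those discontinued under section 2.6.3.

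The cost is a few minutes at visits that already take place, with the existing assessors. Reported counts will probably rise in both arms, and there is some risk of unblinding, so women should be reminded before the question not to disclose their group. If blinded assessors already ask such a question, one or two sentences saying so would settle the point.
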